#### Blood testing

Plasma Aβ42 and Aβ40 levels will be measured at baseline and at 24th week to examine the disease-modifying effects, since the ratio of Aβ42/Aβ40 reflects the AD pathology [15, 16] and associated neurodegeneration, and is related to cognitive impairment [17]. Changes in the ratio of plasma Aβ42/Aβ40 will be compared between the groups. A ratio less than 0.1218 is defined as positive amyloidosis; therefore, the conversion rate to a positive Aβ42/Aβ40 ratio will also be compared. CBC D/C, folate, and vitamin B12 levels will be measured at baseline and 24th week. HDL, LDL, TG, TFT, VDRL, and ammonia levels will be assessed at 1st week.

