### Participants

#### Inclusion criteria

Participants who meet the following criteria will be included: (1) adults aged 55–90 years, with complaints of impaired memory; (2) objective cognitive decline as measured using the Seoul Neuropsychological Screening Battery (SNSB), with a score of 0.5 on the Clinical Dementia Rating (CDR), 3 on the Global Deterioration Scale (GDS), and a normal score on the Korean MMSE (K-MMSE); (3) diagnosed with amnestic MCI by a neurologist; (4) not taking any medication that could affect cognitive function (e.g., gliatilin, gliatamine, ginexin, tanamin, or other psychoactive drugs) within 2 weeks; (4) no change in medication for underlying diseases within 2 weeks, and no expected change in medication during the trial; (5) no difficulty in communication.

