### Statistics

#### Sample size calculation

The primary outcome of interest in this study is the change in the total SNSB-D score between baseline and post-intervention. The calculation of sample size is based on a superiority test, as the aim of this study is to show that KGT is superior to placebo. Our pilot study of aMCI patients treated with KGT showed that the change in the total SNSB-D score was + 22.47, compared to + 8.36 in the placebo group. The calculated effect size (Cohen’s d) was 0.70. Using G*Power software with a power of 0.80 and a two-sided type I error of 0.05, the calculated total sample size for the current study involves 66 participants, with 33 in each group. The dropout rate was 10% (3 of 33 participants) in the previous study; however, since the current study will take a longer follow-up period, we expect the dropout rate to be 20%. We plan to recruit a total of 84 participants for this RCT (42 participants in each group).

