#### Data analyses

An independent professional statistician, who will also be blinded to the allocation, will perform data analyses using SPSS 20.0 software (IBM, Armonk, NY, USA). Efficacy analyses will be performed using the modified intention-to-treat (mITT) and per-protocol (PP) principles. The mITT population will include participants who have completed at least one examination since the beginning of the intervention. The PP population will include participants who will adhere to the trial protocol and undergo all examinations. Missing data will be adjusted using the last-observation-carried-forward (LOCF) imputation method. A safety test will be performed using the ITT principle. The ITT population will include any participants who will take at least one pack of drugs after randomization. To analyze the efficacy outcome and continuous demographic variables, we will perform the Shapiro-Wilk test to confirm the normality of the data distribution. To analyze the fMRI measures and plasma amyloid beta levels, the paired *t*-test will be used for intra-group comparisons and an independent *t*-test will be used for intergroup comparisons, for normally distributed data. Wilcoxon’s signed rank test will be used for intra-group comparisons and the Mann-Whitney U test for intergroup comparisons of non-normally distributed data. To analyze the scores of the neuropsychological test battery, repeated measures of analysis of variance will be used for parametric data, and the Friedman test for non-parametric data. Categorical demographic variables, conversion to normal cognition or dementia, conversion to positive plasma Aβ42/Aβ40 ratio (< 0.1218), and the incidence of AEs between the groups will be analyzed using the Pearson’s chi-square (χ^2^) test or Fisher’s exact test. Continuous demographic variables will be analyzed using the *t*-test or Wilcoxon signed-rank test. All statistical analyses will be two-tailed, and the significance level will be set at *p* < 0.05.

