Next, we will perform multimodal MRI scans in this study, including structural MRI and resting-state and task-evoked functional MRIs. Structural MRI scan of brain atrophy are the most widely accepted markers of AD progression [19]. A decline in hippocampal volume has consistently been related to memory loss in the AD continuum [20]. Since fMRI, which is an indirect measure of brain activity, is useful in the detecting early alterations in brain function, it might be valuable for evaluating the physiological changes over a short time interval [21]. We will investigate the effects of KGT on brain function using both task-based and task-free (resting-state) approaches. Rs-fMRI studies have shown that the progression of memory decline in aMCI is associated with a decline in functional connectivity in DMN regions, which include brain regions related to cognitive function, such as the hippocampus and medial frontal lobe [22]. For task-based fMRI, we will adopt two types of memory paradigms: the face–name association task and the one-back working memory task. By employing cognitive tasks, the fMRI measure will provide information on the changes in brain activity while performing specific activities that mimic the actual difficulties occurring in daily life [21]. Various neuroimaging modalities will be helpful for evaluating the neural underpinning of the effect of KGT.

We will also observe changes in blood-based neuropathological biomarkers, including the plasma levels of Aβ42, which are proposed to reflect the AD pathology and associated neurodegeneration [15–17]. Plasma Aβ levels are correlated with the cerebrospinal fluid (CSF) Aβ levels and Aβ deposition in the brain [23]. Low plasma Aβ42/40 ratios are associated with an increased risk of dementia [24] and greater cognitive decline [25]. We will investigate whether KGT shows any disease-modifying effect via the plasma Aβ42/40 ratio, instead of using CSF biomarkers, which is a costly and invasive process. In addition, plasma Aβ protein levels may provide information about the etiology of MCI.

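### Plasma amyloid is compared between arms without adjustment for the baseline ratio, and conversion to a positive ratio has no stated denominator although participants may already be positive at entry (minor)

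*Protocol article*

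**What the plan says.** Under Inclusion criteria, entry rests on a clinical diagnosis ("diagnosed with amnestic MCI by a neurologist") together with cognitive scales. Neither eligibility list mentions amyloid. Allocation and blinding describes 1:1 blocks of four and names no stratification factor.

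Under Blood testing, plasma Aβ42 and Aβ40 are measured at baseline and week 24, and the change in their ratio is compared between the groups. The categorical outcome follows: "A ratio less than 0.1218 is defined as positive amyloidosis; therefore, the conversion rate to a positive Aβ42/Aβ40 ratio will also be compared". The Discussion gives the purpose: "We will investigate whether KGT shows any disease-modifying effect via the plasma Aβ42/40 ratio".

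Data analyses names an independent t-test for between-group comparison of plasma amyloid, or the Mann-Whitney test if the data are not normal, with no covariate. For the categorical outcome it says: "conversion to positive plasma Aβ42/Aβ40 ratio (< 0.1218), and the incidence of AEs between the groups will be analyzed using the Pearson’s chi-square" (or Fisher's exact test). The efficacy populations are mITT and PP. No subset that is amyloid-negative at baseline is defined, and nothing says that baseline-positive participants are counted either.

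**The concern.** The Background describes amnestic MCI as often a prodromal stage of Alzheimer's disease, so some participants can be expected to have a ratio below 0.1218 on entry. They are not at risk of converting. In a whole-arm rate they are structural zeros: they shrink any true difference, and an accidental excess of them in one arm lowers that arm's rate without any drug effect. The one categorical change open to them, from positive to negative, is not listed.

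The continuous comparison has a milder weakness. The baseline ratio is collected for every participant, yet the named test uses it at most by subtraction. That gives up precision and leaves part of any chance baseline difference in the estimate.

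At stake is how readable a secondary biomarker result will be.

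**Working it through.** **Sample size.** Inputs from Sample size calculation: "The calculated effect size (Cohen’s d) was 0.70"; "Using G*Power software with a power of 0.80 and a two-sided type I error of 0.05". The normal approximation, n per arm = 2(1.96 + 0.84)²/0.70² = 32.0, rounds up to 33, so 66 in total, as stated ("the calculated total sample size for the current study involves 66 participants, with 33 in each group"). The exact noncentral t solution is 33.02, with power 0.7997 at 33 per arm. Dropout of 20% gives 33/0.80 = 41.25, so 42 per arm and 84 in total. The figures reproduce. They concern the SNSB-D score only; no figure is given for conversion.

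**Assumptions for the rest.** The article gives neither baseline positivity (π) nor conversion risk among baseline-negatives (q). I take π = 30 to 70%. The power figures use 33 evaluable per arm.

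**Number at risk.** n(1 − π): of 42 per arm, 29.4 at π = 30% and 12.6 at π = 70%. Of 33, about 23, 16 and 10 at π = 30, 50 and 70%.

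**Dilution.** The whole-arm risk is (1 − π)q, so the whole-arm risk difference is (1 − π)(q₂ − q₁). Power is for Fisher's exact test at two-sided 0.05, by exact enumeration.

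| q in the two arms | π | Whole-arm difference | Power, whole arm | Power, baseline-negatives only |
|---|---|---|---|---|
| 20% v 50% | 0% | 30 points | 0.66 | 0.66 |
| 20% v 50% | 30% | 21 points | 0.40 | 0.46 |
| 20% v 50% | 50% | 15 points | 0.25 | 0.28 |
| 20% v 50% | 70% | 9 points | 0.09 | 0.13 |
| 10% v 30% | 0% | 20 points | 0.42 | 0.42 |
| 10% v 30% | 30% | 14 points | 0.24 | 0.30 |
| 10% v 30% | 50% | 10 points | 0.12 | 0.17 |
| 10% v 30% | 70% | 6 points | 0.03 | 0.06 |

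Restricting the denominator restores the risk difference but adds only about 3 to 6 points of Fisher power, because few participants are at risk either way. The gain is in interpretation.

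**Type I error.** Baseline status precedes randomization, so with equal q both arms have the same expected whole-arm rate. With q = 30% in both arms and π = 30, 50 and 70%, the whole-arm type I error is 0.024, 0.020 and 0.010 (Fisher) and 0.052, 0.053 and 0.055 (Pearson).

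**Chance imbalance.** SD of the between-arm difference in baseline positivity = √(2π(1 − π)/n).
- n = 42: 0.100 at π = 30 or 70%; 0.109 at 50%.
- n = 33: 0.113 at π = 30 or 70%; 0.123 at 50%.
- The chance of an imbalance of 20 points or more is 8 to 10% at n = 33 and 5 to 7% at n = 42.

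For illustration, 60% v 40% positive at baseline with q = 20% in both arms gives 0.20 × 0.40 = 8% v 0.20 × 0.60 = 12%. That is a 4-point difference with no drug effect, or about 3 v 5 of 42 people. An imbalance of this size is about 20/10.9 = 1.8 SD, so it is possible but not typical.

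**Continuous ratio.** Let the ratio have equal variance σ² at both visits and correlation ρ (not given). A t-test on change has variance proportional to 2σ²(1 − ρ); with the baseline as covariate it is σ²(1 − ρ²). The second over the first is (1 + ρ)/2, below 1 for every ρ < 1. A chance baseline difference δ shifts the expected difference in change by (ρ − 1)δ; the covariate removes that shift.

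**The case against.** The strongest reply is that the article never sets a whole-arm denominator. Converting to positive naturally presupposes a negative start, the words about groups name the comparison and not the denominator, and a condensed article may leave the definition to the full protocol or analysis plan. This stands: whole-arm counting is one possible reading. A reader might also infer it because conversion shares a sentence with adverse events and demographics. That sentence shares tests only; efficacy is assigned to mITT and PP, and safety to a separate population.

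A reader might infer that the comparison is biased. The documents do not support this. Amyloid status is fixed before randomization, so only chance imbalance remains, and the error rates above are about nominal or lower.

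A reader might further infer that disease modification is to be judged on conversion. It is not. Blood testing puts the change in the ratio first and conversion is an addition; the abstract lists only the change. The continuous comparison includes baseline-positive participants and captures movement in both directions.

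Nor does the disease-modifying wording amount to an overclaim. Both places state an aim to examine or investigate, not a conclusion.

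What survives is narrower. The conversion rate needs its denominator stated, and the article does fix an unadjusted test for plasma amyloid where a better one costs nothing.

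**Conclusion.** The point holds, at minor severity. Amyloid status is neither an entry criterion nor a stated stratification factor, and the named between-arm test for plasma amyloid ignores the baseline ratio as a covariate. The conversion rate is undefined in its denominator. If whole arms are used, the risk difference shrinks by the baseline-positive share (30 points to between 21 and 9 in the first scenario), and chance imbalance with an SD of about 10 to 12 points carries into the result.

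These sizes rest on an assumed 30 to 70% baseline positivity and assumed conversion risks. The advantage of covariate adjustment does not depend on them. The primary outcome, the sample size and the safety analysis are untouched.

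**What to change.** In Blood testing and Data analyses:

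1. Make the week-24 Aβ42/Aβ40 ratio, compared between arms with the baseline ratio as covariate (ANCOVA), the main amyloid analysis in place of the unadjusted test. If residuals are clearly non-normal, use a log-transformed ratio or a rank-based analysis of covariance.
2. Define conversion as a week-24 ratio below 0.1218 among participants whose baseline ratio is 0.1218 or more. Report it by arm with its denominator.
3. Beside it, report baseline positivity by arm and the reverse shift among those positive at baseline. Treat items 2 and 3 as descriptive support.

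Describing the aim as an on-treatment change in plasma Aβ42/Aβ40 is optional.

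The cost is a few sentences, settled before unblinding, with no new samples or visits. The drawback is a smaller denominator for conversion, which only makes visible how few participants inform it. The adjusted analysis uses one degree of freedom.

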#### Safety assessment

ECG and blood tests will be conducted to examine the safety outcomes. ECG will be conducted at baseline and 24th week. Blood levels of Na, K, Cl, AST, ALT, BUN, Cr, glucose, LDH, CPK will be measured at baseline, 12th, and 24th week. Vital signs will be checked at each visit. We will closely monitor any abnormal findings in vital signs, blood tests, and ECG.

### Adverse events (AEs)

Adverse events will be monitored at each visit, and by telephone, weekly during the intervention and biweekly for 12 weeks after the intervention. All AEs will be assessed for causality and severity, and the details of each AE will be recorded in CRF. If a serious adverse event (SAE) occurs, the participation will be terminated, and the institutional review board (IRB) will be reported as soon as possible. All AEs will be monitored until they stabilize.

### Data management and monitoring

Data will be entered into the electronic case record form (eCRF) by CRC and the investigators. The entered data will be monitored by CRAs, through the process of source data validation (SDV). Only the monitoring agent and the investigators will have access to the dataset. The eCRF files will be stored in the password-secured database called MyTrial. All procedures will comply with the confidentiality standards for medical data. All documents and collected data will be kept for 3 years after completion of the study, after which they will be destroyed. The data will be managed by a data management project manager (DMPM) and a data management associate (DMA), according to standard operating procedures (SOPs). The trial will be monitored by a monitoring committee which is composed of PM, CRA and clinical research manager (CRM). Auditing will be conducted by the Korean Ministry of Food and Drug Safety and IRB.

### Statistics

#### Sample size calculation

The primary outcome of interest in this study is the change in the total SNSB-D score between baseline and post-intervention. The calculation of sample size is based on a superiority test, as the aim of this study is to show that KGT is superior to placebo. Our pilot study of aMCI patients treated with KGT showed that the change in the total SNSB-D score was + 22.47, compared to + 8.36 in the placebo group. The calculated effect size (Cohen’s d) was 0.70. Using G*Power software with a power of 0.80 and a two-sided type I error of 0.05, the calculated total sample size for the current study involves 66 participants, with 33 in each group. The dropout rate was 10% (3 of 33 participants) in the previous study; however, since the current study will take a longer follow-up period, we expect the dropout rate to be 20%. We plan to recruit a total of 84 participants for this RCT (42 participants in each group).

#### Data analyses

An independent professional statistician, who will also be blinded to the allocation, will perform data analyses using SPSS 20.0 software (IBM, Armonk, NY, USA). Efficacy analyses will be performed using the modified intention-to-treat (mITT) and per-protocol (PP) principles. The mITT population will include participants who have completed at least one examination since the beginning of the intervention. The PP population will include participants who will adhere to the trial protocol and undergo all examinations. Missing data will be adjusted using the last-observation-carried-forward (LOCF) imputation method. A safety test will be performed using the ITT principle. The ITT population will include any participants who will take at least one pack of drugs after randomization. To analyze the efficacy outcome and continuous demographic variables, we will perform the Shapiro-Wilk test to confirm the normality of the data distribution. To analyze the fMRI measures and plasma amyloid beta levels, the paired *t*-test will be used for intra-group comparisons and an independent *t*-test will be used for intergroup comparisons, for normally distributed data. Wilcoxon’s signed rank test will be used for intra-group comparisons and the Mann-Whitney U test for intergroup comparisons of non-normally distributed data. To analyze the scores of the neuropsychological test battery, repeated measures of analysis of variance will be used for parametric data, and the Friedman test for non-parametric data. Categorical demographic variables, conversion to normal cognition or dementia, conversion to positive plasma Aβ42/Aβ40 ratio (< 0.1218), and the incidence of AEs between the groups will be analyzed using the Pearson’s chi-square (χ^2^) test or Fisher’s exact test. Continuous demographic variables will be analyzed using the *t*-test or Wilcoxon signed-rank test. All statistical analyses will be two-tailed, and the significance level will be set at *p* < 0.05.

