An independent clinical pharmacist will distribute the granules to participants in each group. Participants will be instructed to dissolve the granules in a glass of warm water and take the solution 30 minutes before or between meals, thrice daily. The investigators and CRC will make weekly reminder phone calls to the participants during the intervention period, in order to help them adhere to medication schedule. Participants will be allowed to take drugs for underlying medical conditions during the study period; however, they will not be allowed to take any medicine that may affect cognitive function. They will be required to report all the drugs taken during the study period. The name and dosage of the medication will be recorded in the case report form (CRF). Participants will be asked to return the leftover drugs at each study visit, and the number of returned drugs will be counted for assessing drug compliance. Those who take less than 80% of study medication will be withdrawn from the study.

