### Assessment

#### K-MMSE and SNSB

K-MMSE will be performed at the screening visit and at 12th week for evaluating the general cognitive status. It is one of the most widely used screening tests to estimate the cognitive functioning [12]. SNSB-II will be conducted at baseline, 24th week, and 36th week, to measure the effect of KGT on cognitive function. Changes in the mean SNSB scores will be analyzed as a primary outcome. SNSB is a neuropsychological test battery most commonly used in South Korea to estimate global cognitive function. The test is composed of various cognitive subtests that assess five domains: memory, attention, language, visuospatial function, and executive function. It also includes other related tests including CDR, K-MMSE, Korean-Instrumental Activities of Daily Living (K-IADL), Barthel-Activities of Daily Living (BADL), and Short-form Geriatric Depression Scale (SGDS) [13]. We will use a modified version of SNSB for dementia (SNSB-D), to obtain a global cognitive function (GCF) score, which is the sum of all the test scores of five domains. The maximum GCF score is 300 points: 150/300 (50%) for memory, 17/300 (6%) for attention, 27/300 (9%) for language, 36/300 (12%) for visuospatial function, and 70/300 (23%) for frontal/executive function [14]. The detailed contents of SNSB-D are presented in Table 3.

**Table 3 Tab3:** Contents of Seoul Neuropsychological Battery for dementia (SNSB-D)

Domains (total score)	Subtests	Maximum points
Attention (17)	Digit span forward	9
	Digit span backward	8
Language & related function (27)	K-BNT	15
	Calculation	12
Visuospatial function (36)	RCFT copy	36
Memory (150)	Orientation	6
	SVLT free/delayed recall	48
	SVLT recognition	12
	RCFT free/delayed recall	72
	RCFT recognition	12
Frontal/Executive function (70)	Motor impersistence	3
	Contrasting program	3
	Go-no-go test	3
	Fist-edge-palm	3
	Luria loop	3
	Categoric word generation	20
	Phonemic word generation	15
	Stroop test-color reading	20
GCF score		300

*K-BNT* Korean short version of the Boston Naming Test, *RCFT* Rey Complex Figure Test, *SVLT* Seoul Verbal Learning Test, *GCF* Global cognitive function

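### No efficacy analysis is defined on all randomised participants, and entry to the mITT set turns on an undefined examination

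*Protocol article*

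**What the plan says.** Under Data analyses, the protocol states: "Efficacy analyses will be performed using the modified intention-to-treat (mITT) and per-protocol (PP) principles". The two sets are then defined: "The mITT population will include participants who have completed at least one examination since the beginning of the intervention", and "The PP population will include participants who will adhere to the trial protocol and undergo all examinations". A third set is kept for harms: "A safety test will be performed using the ITT principle", where "The ITT population will include any participants who will take at least one pack of drugs after randomization". Missing data are to be filled by LOCF.

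On timing, the K-MMSE and SNSB section says "SNSB-II will be conducted at baseline, 24th week, and 36th week". The same section puts a K-MMSE at week 12, and Safety assessment puts blood chemistry at weeks 12 and 24 and vital signs at every visit.

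On leaving the trial, the Intervention section says "Those who take less than 80% of study medication will be withdrawn from the study". Drop-out criteria and Adverse events (AEs) add withdrawal for severe or serious adverse events, and Drop-out criteria also lists use of additional cognition-improving medication. For sample size, "we expect the dropout rate to be 20" per cent, against 10% in the pilot.

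**The concern.** Both efficacy sets are defined by what happens after randomisation. The only set named ITT is used for safety and depends on having taken a dose. The trial is presented as confirmatory, yet none of its efficacy analyses is defined on the groups that randomisation created.

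The weakness is sharper here than in many mITT designs, for two reasons. First, the sized outcome, change in SNSB-D, is not re-measured until week 24, so the choice of qualifying examination decides whether early leavers are in or out. Second, the withdrawal rules respond to tolerability, compliance and use of other cognitive treatment, any of which may differ between KGT and placebo. At stake is whether the KGT–placebo comparison keeps the protection of randomisation, and whether the set's size can be known before unblinding.

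**Working it through.** **Inputs.** From Sample size calculation: 84 planned, 42 per arm; pilot mean changes +22.47 (KGT) and +8.36 (placebo); d = 0.70; power 0.80; two-sided alpha 0.05; dropout 10% in the pilot and 20% expected. From K-MMSE and SNSB: SNSB at baseline, week 24 and week 36.

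**The plan's own figure.** Per arm, 2 × ((1.960 + 0.842)/0.70)² = 32.04, rounded up to 33, so 66 in total. An exact t calculation gives power 0.7997 at 33 per arm. For dropout, 33/0.8 = 41.25, rounded up to 42 per arm, so 84. The stated sizes reproduce and are not in dispute. The 66 is close to 84 × 0.8 = 67.2, so the trial was sized on participants with outcome data.

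**Reading A: the examination is the SNSB.** Anyone with neither a week-24 nor a week-36 SNSB is out.
- At 10% loss before week 24: 84 × 0.10 = 8.4, about 8 excluded.
- At 20% loss, all before week 24: 84 × 0.20 = 16.8, about 17 excluded.

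**Reading B: any examination counts.** Vital signs at a visit, or the week-12 K-MMSE or chemistry, would qualify. Those who leave before the qualifying visit are still excluded. Those who leave after it but before week 24 are kept, and the only SNSB available to carry forward is the baseline, so their change is 0. With every leaver kept and scored in this way:
- 20% loss in each arm: 0.8 × (22.47 − 8.36) = 11.29, against 14.11 without loss; d about 0.59, power about 0.76.
- 30% loss on KGT, 10% on placebo (assumed): 0.7 × 22.47 − 0.9 × 8.36 = 8.20.
- 10% on KGT, 30% on placebo (assumed): 0.9 × 22.47 − 0.7 × 8.36 = 14.37.

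So the estimate moves with the balance of dropout, and not only with the drug.

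**Illustration of bias under Reading A, with no drug effect.** Implied SD = 14.11/0.70 = 20.2. Assume that KGT leavers would have changed 10 to 20 points less than KGT stayers, and that placebo leavers are a random subset. Dropping the leavers creates a spurious difference of (fraction lost) × (10 to 20). The two-sided t-test then rejects as follows.

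| Loss before week 24 | Stayers per arm | Spurious difference | d | Type I error |
|---|---|---|---|---|
| 10% | 37.8 | 1 to 2 points | 0.05 to 0.10 | 5.5% to 7.1% |
| 20% | 33.6 | 2 to 4 points | 0.10 to 0.20 | 6.9% to 12.6% |

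The 10–20 points and the one-sided pattern of dropout are assumptions; the documents give no figure for either.

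**The case against.** **Timing of dropout.** The protocol raises dropout from 10% to 20% because follow-up is longer. The pilot also treated for 24 weeks, and the Discussion says it had no cognitive follow-up after treatment. The natural reading is about 10% lost by week 24 and the rest between weeks 24 and 36. Those later leavers have a week-24 SNSB and are in mITT on either reading. This stands: the 20% row is an upper case.

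**Direction and size.** A reader might infer that the planned analysis overstates the effect by 25% or even 47%. The first figure compares 14.11 among stayers with 0.8 × 22.47 + 0.2 × 8.36 − 8.36 = 11.29, which assumes that KGT leavers would change like placebo. The second compares it with 0.8 × 22.47 − 8.36 = 9.62, which gives KGT leavers no change and placebo leavers the full placebo gain. Both need all 20% lost before week 24. At 10% they fall to 11% (14.11/12.70) and 19% (14.11/11.86). Nothing in the documents shows that dropout is informative on KGT only; the pilot is reported as well tolerated, with high adherence. On Reading B with equal loss, LOCF dilutes the effect. No direction of bias can be claimed.

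**Overlap with PP.** It is tempting to say that mITT shrinks to week-24 completers, so that PP is no check on it. That goes too far. A participant who missed week 24 but attended week 36 is in mITT, and PP requires all examinations, so those lost between weeks 24 and 36 separate the two sets.

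**Safety by product taken.** A reader might object that an ITT rule counts harms under the wrong product. The set is already defined by dosing, and the protocol does not say how a participant given the wrong product would be classified. Only the name is at fault.

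**Condensed article.** The schedule table is not shown, and a fuller definition may exist elsewhere. But the article does not leave the sets open: it defines them, and does so without all randomised participants.

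**Conclusion.** The point holds. As written, efficacy is analysed only in sets conditioned on events after randomisation, and early leavers are either excluded or, if retained without a later SNSB, scored as unchanged, depending on how one undefined word is read. On the SNSB reading the exclusion is about 8 of 84 at the pilot's dropout and at most about 17 at the planned rate.

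The size of any resulting bias is unknown. The type I error figures of about 5.5–7% and 7–13% illustrate what informative dropout in one arm could do; they do not predict what this trial will do. The sample size is unaffected. This should be corrected before unblinding, but it does not undermine the design.

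**What to change.** 1. Define the primary efficacy set as all randomised participants in the arm assigned, whatever examinations they complete.
2. Analyse SNSB-D at baseline, week 24 and week 36 with a likelihood-based longitudinal model that has a baseline mean common to both arms, in place of LOCF. Participants with a baseline only then stay in the analysis, under a stated missing-at-random assumption.
3. Keep the present mITT and PP sets as sensitivity analyses, and state which examination qualifies for mITT.
4. Add a sensitivity analysis for dropout not at random, for example with KGT leavers assumed to change like placebo. It is needed because a baseline-only participant carries almost no information on the week-24 contrast. In that scenario the model would still estimate a difference near the 14.11 seen among stayers and not 11.29.
5. Rename the dosed set, now called ITT, the safety set.

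The cost is wording in the analysis plan and slightly more analysis work, with no extra visits or participants. The sensitivity analyses may show a smaller effect.
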